### Data management

A paper case report form (CRF) will be developed before commencing the study. Patient information will be recorded using the CRF. The data manager will verify the CRF data, which will then be entered into a data management system. Doubtful data will be provided to the researchers for verification. Patient-identifying information, such as name, telephone number, and home address, will not be entered into the data management system. The verified data will be sent to statisticians for statistical analysis.

Some useful measures are often used to minimize the occurrence of lost follow-up. Firstly, a clinical nurse will be arranged to maintain long-term contact with the patien, and save information on commonly used contact methods of the patient such as telephone number, WeChat, email address, among others. In addition, the nurse will be in contact with the patient every other day to monitor the patient for immune-related adverse reactions. When the patient reports an adverse reaction, the nurse will promptly report it to the doctor, who will then contact the patient and give reasonable treatment. At the same time, it is also very important to save the contact information of at least one family member of the patient, so that the patient can be contacted in a timely manner.

### Statistics

#### Determination of sample size

Based on the data from the KEYNOTE-042 study, the median PFS of the target subjects receiving the trial treatment in this study is expected to be 6 months. The enrollment time is 1.5 years, and the follow-up time is 1 year. The type I error rate is 5%, and the power is 80%. Considering a 10% abscission rate, the current study will include 30 patients with advanced NSCLC with COPD.

#### Planned analyses

The mean, standard deviation, median, quartile, and maximum and minimum values will be calculated for measurement data. Frequency and percentage will be calculated for counting data. Paired-samples t-test and the Wilcoxon rank sum test will be performed to compare before- and after-treatment measurements for normal and non-normal distributions, respectively. The Kaplan-Meier method will be used to estimate the median progression-free time and its 95% confidence interval. Full analysis set (FAS) and per protocol set (PPS) will be used to analyze the efficacy indexes, and safety set (SS) will be used to analyze the safety data. Statistical significance will be set at p-value < 0.05.

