## Methods

### Study design

This study was designed as a single-arm, single-center, prospective, phase II clinical study. It will include 30 advanced (stage IV) NSCLC combined with COPD primary treatment subjects. The diagnosis of each subject will be confirmed by clinical, radiographic, pathologic, and pulmonary function evaluation. Patient recruitment was initiated in November 2022, and we plan to complete the study in December 2024. This trial has been approved by the Institutional Review Board of Tian Chest Hospital (Approval date: August 25, 2022 and approval number: 2022KY-012-01) and has been registered in the clinicaltrials.gov database (NCT05578222). A schematic diagram of the trial is presented in **Figure 1**.

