### Outcome measurements

The primary outcome is PFS, defined as the time from randomization initiation to the progression of tumor or death for any reason (refer to RECIST v1.1).

The secondary outcomes include objective response rate (ORR), overall survival (OS), rate of acute COPD exacerbations (times/year), lung function, mMRC score, CAT score, impact of treatment on patient’s health-related quality of life (HRQoL), antibiotic use (including duration and classes), and AEs associated with immune checkpoint inhibitors. ORR is defined as the proportion of patients with complete response (CR) and partial response (PR) and is used to estimate the treatment efficacy according to RECIST v1.1. OS was measured as the period from the diagnosis of lung cancer to death. Acute exacerbation was defined if respiratory tract symptoms such as cough, sputum production, and dyspnea were significantly worse than usual, and the treatment program had to be adjusted, such as by using oral or intravenous glucocorticoid treatment combined with or without antibiotics, while excluding pneumothorax, heart failure, pneumonia, and other diseases. Acute exacerbations of COPD are classified as Grades I-III according to clinical symptoms.

Exploratory endpoint is to explore the association between COPD grade and the degree of immune cell (CD4+ T lymphocytes and CD8+ T lymphocytes) infiltration, as well as the association between COPD grade and the efficacy of immune checkpoint inhibitors.

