Baseline tumor imaging evaluation will be completed within 2 weeks of initial treatment. Imaging evaluation will be performed every 6 weeks for 6 months from the first pembrolizumab dose and approximately every 12 weeks thereafter until disease progression or early withdrawal. The anti-tumor efficacy will be evaluated according to RECISTv1.1 and irRC (23).

Pembrolizumab-related AEs will be determined after each treatment cycle. The severity of AEs will be determined according to NCI-CTC AE 5.0. Investigators will be responsible for the appropriate measurement of AEs and will determine the relationships between AEs and the study drugs. AEs will be followed up until they were grades 0 to 1 or stabilized or returned to baseline levels. COPD status will be evaluated every 3 months according to pulmonary function, GOLD grading, mMRC score, CAT score, ABCD grouping, and AECOPD severity (24).

HRQoL will be assessed by completing the European Organisation for Research and Treatment of Cancer core quality of life questionnaire (QLQ-C30) at baseline, evaluation visits, end-of-treatment visits, and safety follow-up visits (within 30 d after the last dose).

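### The plan names the Wilcoxon rank sum test, an independent-samples test, for non-normal before/after measurements on the same patients; the signed-rank test is the paired counterpart

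*Protocol article*

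**What the plan says.** Under Planned analyses, the protocol article states: "Paired-samples t-test and the Wilcoxon rank sum test will be performed to compare before- and after-treatment measurements for normal and non-normal distributions, respectively". The word *respectively* gives the paired t-test to normal data and the rank sum test to non-normal data, for one and the same task.

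Under Study design: "This study was designed as a single-arm, single-center, prospective, phase II clinical study". There is no second group.

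Under Study schedule and assessments: "COPD status will be evaluated every 3 months according to pulmonary function, GOLD grading, mMRC score, CAT score, ABCD grouping, and AECOPD severity". Table 2 places lung function and the COPD assessments at screening, every 3 months on treatment and at the end-of-treatment visit. It places QLQ-C30 at screening, before each cycle, at end of treatment and at safety follow-up. Under Outcome measurements, lung function, mMRC, CAT and health-related quality of life are secondary outcomes.

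The primary outcome, PFS, has its own method: "The Kaplan-Meier method will be used to estimate the median progression-free time and its 95% confidence interval".

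**The concern.** In a single-arm trial every before/after comparison is within patient. Normality decides between a parametric and a rank-based test; it does not decide whether the data are paired. The sentence nevertheless treats the same data as paired when they are normal and as two independent samples when they are not. Nothing else in the article corrects this.

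The rank sum test takes its null variance from two independent groups. When a patient's later value tends to resemble the earlier one, the true variance of the comparison is smaller, so the test rejects too rarely.

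The measures that may be affected bear on a stated reason for the trial. The Introduction says earlier work suggested that checkpoint inhibitors could aggravate lung damage and COPD symptoms, and that those studies lacked measures such as mMRC and CAT. If the rank sum test is run on those scores, a real worsening could go undetected.

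**Working it through.** **Inputs from the protocol article**

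- Design: single arm, repeated measurement of the same patients (Study design; Study schedule and assessments).
- Number of pairs: "Considering a 10% abscission rate, the current study will include 30 patients with advanced NSCLC with COPD". Removing 10% gives 30 × 0.9 = 27.
- Significance level: 0.05 (Planned analyses), taken here as two-sided.
- The article states no power, effect size or sample size for the before/after comparisons, so there is no figure of the plan's own to reproduce on this point.

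**Assumptions**

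- The within-patient correlation ρ is not given and is varied from 0 to 0.9.
- The shift, in SD units, is set so that the signed-rank test has about 80% nominal power: δ = (1.96 + 0.84) × √(2(1 − ρ)) / √(27 × 3/π). This gives 0.780 at ρ = 0, 0.552 at ρ = 0.5 and 0.247 at ρ = 0.9. The paired t-test has 78% to 80% power at these shifts.

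**Step 1: direction, by a normal approximation**

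For independent groups of size n the difference in means has variance 2σ²/n. For pairs it is 2σ²(1 − ρ)/n. A test that uses the first when the second is true has approximately

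- type I error = 2Φ(−1.96/√(1 − ρ))
- power at the shift above = Φ(2.80 − 1.96/√(1 − ρ))

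At ρ = 0.5, 1.96/√0.5 = 2.77, so type I error is 2Φ(−2.77) ≈ 0.006 and power is Φ(0.03) ≈ 0.51. At ρ = 0.7, 1.96/√0.3 = 3.58, so power is Φ(−0.78) ≈ 0.22. At ρ = 0 the formulas return 0.05 and 0.80, which means no loss.

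**Step 2: simulation**

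4,000 runs per setting, 27 pairs, bivariate normal data:

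| ρ | Rank sum type I error | Rank sum power | Signed-rank power | Share of power lost |
|---|---|---|---|---|
| 0 | 0.049 | 0.784 | 0.776 | none |
| 0.3 | 0.020 | 0.653 | 0.771 | 15% |
| 0.5 | 0.008 | 0.494 | 0.771 | 36% |
| 0.6 | 0.004 | 0.379 | 0.782 | 52% |
| 0.7 | 0.002 | 0.230 | 0.770 | 70% |
| 0.8 | 0.000 | 0.090 | 0.770 | 88% |
| 0.9 | 0.000 | 0.006 | 0.760 | 99% |

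The share lost is 1 − (rank sum power / signed-rank power); at ρ = 0.5, 1 − 0.494/0.771 = 0.36. The type I error of the signed-rank test stays between 0.043 and 0.051.

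**Step 3: sensitivity**

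- A slightly larger shift, √(2(1 − ρ)) × 2.93/√27, gives rank sum power of 51%, 26% and 0.5% at ρ = 0.5, 0.7 and 0.9, against 79%, 78% and 79% for signed-rank.
- Lognormal data at the Step 2 shifts give rank sum versus signed-rank power of 0.474 vs 0.702 at ρ = 0.5, 0.220 vs 0.697 at 0.7 and 0.007 vs 0.702 at 0.9. At ρ = 0 the rank sum test is not worse (0.774 vs 0.717).
- Using 30 pairs gives the same pattern.
- Coarse ordinal scores such as mMRC were not simulated. The figures show direction and rough size for those, not exact power.

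**The case against.** The strongest reply is that this is a naming slip. The sentence sets the test beside the paired t-test and limits both to before/after data, so the authors evidently regarded the data as paired. The SAP is not shown, and the test actually programmed may be the right one. That is plausible, but the article names a specific test and the name is wrong. Anyone who programs from the text would run an independent-samples test, so the wording needs correcting either way.

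Three stronger readings are tempting, and the documents do not support them.

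- *That most of the power is lost.* This holds only from a correlation of about 0.6 upward. The documents give no correlation, and at 0.3 the loss is about 15%.
- *That the COPD safety result as a whole would be falsely reassuring.* The rank sum test applies only to measures judged non-normal, and the article does not say which these will be. Exacerbation rate and immune-related adverse events are separate secondary outcomes and are not evidently before/after measurements. Descriptive summaries are also planned.
- *That early dropout undermines the before/after comparison, so a mixed model is required.* Table 2 collects lung function, COPD assessments and QLQ-C30 at the end-of-treatment visit. Patient withdrawal keeps withdrawn patients in follow-up unless they withdraw consent and refuse it. How to model the repeated measurements is commonly left to the SAP, and its absence from an article is not an error.

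**Conclusion.** The point holds: an independent-samples test is assigned to paired data. The direction of the error is clear for any positive within-patient correlation. The test is conservative and does not inflate false positives; its cost is missed change. The size depends on the assumed correlation, from no loss of power at 0 to nearly all of it at 0.9, for about 27 pairs and one chosen shift.

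The reach is limited to secondary before/after measures judged non-normal. The Kaplan-Meier analysis of PFS does not use this test. The sample size of 30 is set from an expected median PFS and is not affected. This should be fixed before analysis, but it does not threaten the trial's main result.

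**What to change.** In Planned analyses, and in the SAP if it repeats the sentence, replace the Wilcoxon rank sum test with the Wilcoxon signed-rank test for all within-patient comparisons. Check that the analysis program calls the paired version.

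The cost is one term in one sentence. No new data, patients or visits are needed.

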#### Trial status

This trial is open for recruitment. The first patient was enrolled in February 2023, after all legal approvals required in China were received.

## Discussion

Currently, immune checkpoint inhibitors are the standard first-line treatment for patients with stage IV driver-negative NSCLC. However, evidence-based medical use of first-line immunotherapy for NSCLC does not consider COPD, which may affect the efficacy and safety of the treatment. Currently, the first-line standard treatment option for patients with NSCLC complicated with COPD remains unclear and relies on the treatment of NSCLC alone. To date, a limited number of retrospective studies have explored the efficacy and safety of immunotherapy in patients with NSCLC complicated with COPD. Therefore, this prospective, single-arm phase II clinical study was designed to explore the efficacy and safety of first-line immunotherapy in patients with NSCLC complicated with COPD. We expect that the results of this phase II study will provide preliminary evidence for future randomized controlled clinical trials on the use of first-line immunotherapy for NSCLC complicated with COPD.

## Ethics statement

This trial has been approved by the Institutional Review Board of Tian Chest Hospital (Approval date: August 25,2022 and approval number: 2022KY-012-01). All subjects provided written informed consent.
